## 2. ROLES & RESPONSIBILITIES OF TRIAL MANAGEMENT COMMITTEES/ GROUPS & INDIVIDUALS

[name] will lead the trial and take overall responsibility, supported at NMAHP-RU by [name] & [name] as experienced Trial Managers (job-share) and grant-holders: [name] (deputy for PH), [name] (qualitative oversight); [name] (SMS and health psychology lead who holds an honorary researcher position at Stirling) and [name] (NMAHP-RU trial statistician/methodologist). [name], [name] and [name] will be Centre leads. CHaRT registered CTU ( Director [name]), University of Aberdeen, will provide Senior Trial Manager input ([name]) and will lead randomisation, data management, analysis and database programming working closely with [name] (HIC, University of Dundee) who will continue to deliver the SMS+I interventions and participant tracker software which worked well in the Feasibility Study. [name] (Aberdeen, senior health economist) will lead the health economic analysis. [name], [name] (Public Health Methodologist) and [name] will contribute obesity, public health and incentive trial expertise, with [name] from Men's Health Forum GB, [name] and [name] from Men's Health Forum All Ireland contributing Public and Patient Involvement.

***Centre Management Meetings:*** fortnightly/monthly (depending on stage of trial) with the Centre Leads, Fieldworkers and the trial managers, with others invited when required.

***Co-Investigator Project Management Team Teleconferences:*** as required every 2-4 months, with email updates between. Grant holders are involved in overseeing all aspects of study conduct.

***The Programming, Statistics, Health Economics and Data Team*** will consist of [name], [name], [name], [name], [name], Trial Managers, [name] and [name]. Meetings will take place monthly in Phase 1, and every 1-3 months thereafter, with email and teleconferences as required. [name] will lead the statistical analysis plan, oversee the statistician undertaking the statistical analysis at CHaRT and the statistical tables for the report and papers. The CHaRT statistician will conduct the final analysis blind to group allocation, produce data for reports and publications. The CHaRT team includes a senior trial manager, senior IT support, a programmer and quality assurance staff.

***The Qualitative Team*** will be overseen by [name] supervising [name], qualitative Research Fellow (RF), who will be the lead at Stirling, with [name], [name], [name], [name], [name], Centre RAs, the Trial Managers, PPI from Men's Health Forum and [name]. Meetings will take place: early in the trial to plan data collection; in stage 2 to finalise the thematic framework and coding index; and to interpret the findings for report writing. Teleconferences will be held as required.

## 2.1. Trial Management Committees

The committees involved in trial coordination and conduct are documented in the Trial Steering Committee Charter. The Co-Investigators are listed on <https://fundingawards.nihr.ac.uk/award/NIHR129713> and both Co-investigators and trial staff will be listed on [www.gameofstonesresearch.com](http://www.gameofstonesresearch.com)

***Trial Steering Committee (TSC)*** (includes data monitoring role as agreed with NIHR)

The Independent TSC will meet at least annually face to face or online as required to oversee all aspects of the trial, with accountability to the funder and the sponsor. As this trial involves a low-risk self-management intervention, the TSC will also fulfil the role of monitoring safety and make recommendations as to any modifications that are required to be made to the protocol or the termination of all or part of the trial. Six independent members have agreed to join. A Trial Statistician and methodologist (continuing as chair from the previous Feasibility Study); a Public Health expert in obesity trials; a Public Health Local Authority Commissioner; a Health Economist and two lay members with expertise in Men's Health. A Charter based on HRA guidance will be signed by members and updated as required.

TSC roles will be to review the protocol and assess two stage traffic light monitoring as recommended in guidance.

i) progression criteria after 4 months of recruitment, for % of total target sample size achieved:

- Green: >50% of target sample size after 4 months. Proceed.
- Amber: 25-49% modify recruitment strategies:
- Red: <25% consider stopping in discussion with the funder and the sponsor

ii) progression criteria in ~study month 34 will be for the TSC to decide if a clinically significant difference in the primary outcome has been met for at least one comparison. The TSC in discussion with NIHR may consider other core outcome criteria e.g. absolute weight change (kg); health inequalities; % of men achieving  $\geq 5\%$  or  $\geq 10\%$  weight loss. If NIHR agreed criteria are met, we will progress to Phase 3 and complete: 24M data collection and analysis; stakeholder scalability interviews; full effectiveness and cost-effectiveness modelling; and plan for future data linkage. If criteria are not met, the study could end before 42 months. If the study does end before all 24M follow-up data has been collected, existing data will be analysed.

### ***Project Management Group***

The Project Management Group (PMG) consists of the NIHR Grant holders <https://fundingawards.nihr.ac.uk/award/NIHR129713> with key trial staff (trial managers, research fellows, statistician; programmers) and will meet every 2-4 months remotely as required. They will ensure all practical details of the trial are progressing and working well and everyone within the trial understands them. Observers will be invited to attend at the discretion of the PMG. The PMG will meet/teleconference every three months on average, but monthly in the initial set-up stage.

### ***Trial Coordinating Team***

The trial will be coordinated by the CI and Trial Managers based at NMAHP RU at Stirling University. The Trial Managers will be responsible for the day to day transaction of trial activities (supported by [name], senior trial manager at CHaRT) and coordinating work conducted by the Fieldworkers at each of the 3 centres via their Centre Leads. The Fieldworkers are responsible for day to day recruitment and follow up of participants; data collection and management; liaising with PPI and Stakeholders and assisting the process evaluation team. Two Fieldworkers at each centre will be supported by a pool of postgraduate students, so that recruitment can occur flexibly at weekends and in the evenings, enabling men who work to join the study. This was effective and efficient in the Feasibility Study.

A trial-specific delegation log will be prepared for each centre, detailing the responsibilities of each member of staff working on the trial.

The CI, Trial Managers and Qualitative Research Fellow will meet weekly, with others invited when required. The CI, Trial Managers and Centre Leads will meet fortnightly/monthly (depending on stage of trial), with others invited when required.

### **3. BACKGROUND**

In this randomised controlled trial we are investigating effective and cost-effective interventions that may engage men with obesity to achieve clinically significant weight loss and maintain that weight loss, particularly in areas where there are health inequalities. Men engage less often than women in existing weight loss interventions [3] and sustainable interventions with broad reach are needed for men who do not like or cannot access groups. Yet men die sooner than women and year-on-year mortality improvements have slowed, particularly in disadvantaged areas [4, 5]. Obesity increases the risk of type 2 diabetes, heart disease, stroke, mobility problems and some cancers, leading to multi-morbidity. Weight loss can reduce premature all-cause mortality and reverse the early stages of type 2 diabetes, and therefore reducing obesity is a UK Government priority. Recent Office for National Statistics data demonstrate that obesity and health inequalities are risk factors for worse health outcomes for people with Covid-19.

This proposed trial is therefore important to the public, the NHS and society. In 2017, 27% of men in England were obese; this prevalence is higher than elsewhere in Europe and predicted to increase [6, 7]. In 2017/18, there were 711,000 admissions to English hospitals where obesity was recorded as the primary or secondary diagnosis, a 15% increase from 2016/17 [6, 7].

Recent reports recommend testing innovative, scalable, digital interventions for reducing obesity [8]. Scalable digital interventions like Game of Stones can increase reach to men and promote self-management. They can be offered within current NICE recommended tiered weight management services [9] to span primary, secondary and tertiary disease prevention.

Game of Stones is a parallel, 3-arm RCT which delivers automated SMS (short message system) texts with or without financial incentives and compares weight change at 12 months with a waiting list for SMS, for men with obesity. Our promising Feasibility Study demonstrated broad acceptability. It was over-subscribed and 60% of the 105 men participating lived in the two most disadvantaged Scottish Index of Multiple Deprivation (SIMD) postcode quintiles, which is more than in other UK obesity trials [1, 2, 10]. Fewer men living in disadvantaged areas dropped out compared to men living in more advantaged areas. An independent Trial Steering Committee judged that progression criteria for a full RCT were met and this full RCT will follow a similar trial protocol with some modifications for Covid-19.

#### **3.1. Rationale**

The research question is: Are automated 'Short Message System' (SMS) texts, delivered to support behaviour change, with or without endowment Incentives (I), effective and cost-effective for weight-loss at 12 months compared to a waiting list control in men with obesity?

We have conducted four systematic reviews of the quantitative, qualitative and economic evidence for the management of obesity in men [11]. The rationale for the SMS and incentive interventions in Game of Stones is supported by systematic review evidence. We have completed a systematic review and meta-analysis of 15 RCTs examining SMS-delivered interventions for weight loss (n=12) and weight loss maintenance (n=3) [12]. The weight loss trials had an effect at intervention end (median duration 6 months) with a mean difference -2.28kg (95% confidence interval [CI] -3.18 to -1.36 kg). Men accounted for 41% of trial participants, higher than for other interventions [11], but there were no men-only trials and health inequalities data were not reported. The ROMEO reviews [11] identified that interventions need to be designed with men in the target population. In Game of Stones, we worked closely with Men's Health Forum Charities and men in the target population to write the text messages informed by qualitative data analysis, to ensure the language, content, frequency and timing are acceptable [2].

**INCENTIVES:** Systematic review evidence of financial incentives shows their potential to change habitual behaviours and help reduce health inequalities [13]. Moreover, the evidence for financial incentives for weight loss is growing [14] and deposit contracts can be effective [15]. But deposit contracts, where people put their own money into an account, losing it if weight loss targets are not met, may increase health inequalities for the cash poor. In a discrete choice experiment (DCE) we conducted with 1045 men with obesity to design an incentive, with high uptake across all men [2]. In comparison, this cost is similar to attending commercial weight loss groups; or annual prescribing costs for the weight loss drug Orlistat (excluding clinical appointments and blood test monitoring costs) – which men do not find helpful [11].

Pedometers are given to all participating men in Game of Stones to encourage self-monitoring. All men (including wait-list arm) will have access to a Game of Stones website which includes links to evidence-based information about weight loss, and to charities like Men's Health Forum which support men's physical and mental health.

This trial will recruit from diverse areas in three UK countries to provide generalisable evidence on effectiveness, cost-effectiveness and impact on health inequalities relevant for policy makers and service commissioners. Programming for transferability will involve public service technology experts so that SMS and incentives can in future be delivered centrally or locally, together or separately. Measuring weight by health care assistant or equivalent staff in health or community venues was feasible [2]. This self-care intervention can accommodate future technological advances in digital scales linked to databases to minimise staff resource requirements. Commissioners tell us that variations in effect sizes

by socio-economic group and levels of co-morbidity will be important to inform how Game of Stones might contribute to current weight management services.

In summary, Game of Stones targets a clear evidence gap in weight management services and health inequalities for men. Obesity, health inequalities and prevention are all UK policy priorities in the NHS Long Term Plan ([www.longtermplan.nhs.uk](http://www.longtermplan.nhs.uk)) and are likely to remain so for the foreseeable future, particularly with new evidence emerging about risk factors for Covid-19. In a female dominated weight management landscape, NHS service commissioners want to know whether financial incentives with text messages can make a difference to improve obesity outcomes for men.

The research team were invited to apply for additional funding from NIHR (submitted September 2021) to investigate UK policy priority areas: mental health conditions and multiple long-term conditions within the Game of Stones Trial. A new secondary outcome Patient Health Questionnaire – 4 (PHQ-4) was approved by the Ethics Committee in September 2021 and baseline data commenced. Funding was approved in January 2022 and contract variation signed on 1st March 2022. Adults with obesity are more likely to be depressed than those without [67] and to experience generalised anxiety disorders. [68] Health inequalities are apparent for both people with mental health problems and with obesity, with Covid-19 highlighting disparities. [69] Mental illnesses are associated with a 1.4 to 2-fold increased risk for obesity, diabetes and cardiovascular diseases compared to the general population. [70] The causal pathways for obesity, mental health and health inequalities are complex and multi-directional, and there is an evidence gap for men living with obesity.

There is an evidence gap in existing systematic reviews for men living with MLTC and obesity who participate in weight management intervention trials. [71, 72] Many trials of weight management/dietary change interventions focus on participants with single non-communicable conditions. However a large UK primary care cohort highlights the high prevalence of co-morbidities in patients with Type 2 diabetes. [73] We have undertaken qualitative interviews with 8 senior UK decision makers during the set-up of this trial and diabetes is a priority condition.

Additional exploratory sub-group analyses and mixed method process evaluation are described in detail in the Statistical Analysis Plan and Process Evaluation Plan and will be reported separately from the primary trial effectiveness and cost-effectiveness outcomes. This effectiveness and cost effectiveness trial of Game of Stones will produce evidence that service commissioners, the NHS and the public require.

### **3.2. Assessment and management of risk**

This is very low risk automated digital intervention to support and motivate self-care in men with obesity who want to lose weight. It is a Public Health Trial and not a clinical trial. Recruitment is equitable and

inclusive, open to any member of the general public who meets the eligibility criteria. Adverse events will be reported and monitored as outlined in Section 8 of this protocol.

Research Fieldworkers' safety will follow appropriate guidance from the University where they are employed, and local risk assessments completed where necessary. The researchers may work in pairs when recruiting or work alone, according to the neighbourhood and as advised by stakeholders with local knowledge. Principle Investigators will ensure that centre staff can undertake fieldwork in a Covid-19 safe way.

## **4. OBJECTIVES AND OUTCOME MEASURES/ENDPOINTS**

### **4.1. Research question**

Are automated 'Short Message System' (SMS) texts, delivered to support behaviour change, with or without endowment Incentives (I), effective and cost-effective for weight change at 12M compared to a waiting list control in men with obesity?

### **4.2. Primary objective**

To conduct a 3-arm RCT to estimate between group difference in % weight change at 12M from baseline for men with obesity who receive i) SMS+I; ii) SMS only; iii) 12M wait list for SMS

### **4.3. Secondary objectives**

- To assess differences between groups in secondary outcomes
- To assess the cost-effectiveness of SMS+I and SMS only compared to a wait list control
- To understand men's and service providers' experiences of the intervention
- To follow up men at 24M (12M after texts/incentives cease for the intervention groups; 9 months after the SMS cease for the waiting list group). Request consent for linkage to long-term health outcome data
- To refine the digital programming for future scalability and implementation
- To compare PHQ-4, Warwick and Edinburgh Mental Wellbeing Scale (WEMWBS), Quality of Life (EQ-5D-5L-AD) Anxiety and Depression (AD) dimension and Weight Self-Stigma Questionnaire (WSSQ) measures for the 3 trial groups at baseline and 12 months
- To undertake exploratory moderator analyses examining interactions between mental health/wellbeing status at baseline and 12-month weight change
- To undertake exploratory mixed methods analyses examining mental health/wellbeing status, weight change trajectories, health inequalities, lived experiences and views to inform implementation, tailoring and future research
- To undertake exploratory moderator analysis for weight change at 12 months by the presence/absence of multiple long-term conditions (with and without diabetes) at baseline
- To compare secondary Quality of Life, mental health/wellbeing outcomes for men with or without MLTC at baseline
- To undertake exploratory mixed method analyses to understand the lived experiences of men with MLTC and what would make a difference for recruitment, implementation, tailoring and future weight management interventions.
- To undertake a mixed method process evaluation to inform future implementation and research

## 4.4. Outcome measures/endpoints

### 4.4.1 Primary endpoint/outcome

Demographics and outcome measures (Table 1) are based on the FFIT trial [16], and the recently published STAR-LITE core outcome set for behavioural weight management interventions [17].

**The Primary outcome** is within-participant change from baseline weight expressed as a percentage of baseline weight at 12 months from baseline. The trial is powered on a 3% weight loss, which NICE states is clinically significant and consistent with STAR-LITE Core Outcome set for obesity trials [17].

### 4.4.2 Secondary endpoints/outcomes

**Secondary outcomes at 12 months:** absolute weight change from baseline (kg); % of participants achieving 0<5% weight loss; ≥5<10% weight loss; % of participants achieving ≥10% weight loss, % of participants losing any weight, % of participants gaining weight; EQ-5D-5L; EQ-5D-5L-AD; WEMWBS; PHQ-4; WSSQ.

**Health economic outcomes:** NHS costs, QALYs, incremental cost-per QALY gained and incremental cost per % weight loss over trial follow-up and modelled lifetime.

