### **9.3.3 Secondary outcome analysis**

Secondary and exploratory outcome measures will be analysed similarly, using an appropriate generalised linear model, including binary logit regression for dichotomous outcomes (e.g. smoking status) and ordered logit for ordinal outcomes (e.g. alcohol intake). Statistical significance will be at the 2.5% level, consistent with the assumptions made in the sample size calculation. Descriptive summaries of process outcomes will be reported but no formal analysis of these data will be undertaken.

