## **9.8. Other statistical considerations.**

The final approved version of the Statistical Analysis Plan will be publicly available at the end of the trial. This will be accompanied by a summary of changes made from the original version and the final approved version. We will also report any aspects of the analysis which have deviated from the SAP along with a justification for the deviation.

One other consideration is that the TSC in discussion with NIHR may consider other core outcome criteria in addition to the primary outcome when deciding about progression to Phase 3. This will include the following secondary outcome measures: absolute weight change (kg); % of participants achieving  $\geq 5\%$  weight loss; % of participants achieving  $\geq 10\%$  weight at 12M from baseline.

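### The ≥5% weight-loss outcome that Section 9.8 calls secondary is missing from Section 4.4.2, which lists bands instead; if tested separately, the lowest band has no fixed direction of benefit

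*Protocol*

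**What the plan says.** Protocol Section 4.4.2 lists, among the secondary outcomes at 12 months, the percentage "of participants achieving 0<5% weight loss; ≥5<10% weight loss; % of participants achieving ≥10% weight loss", followed by the percentage "of participants losing any weight, % of participants gaining weight". The trial summary in Section 1 uses the same split at 5% and 10%. Neither place lists a cumulative ≥5% outcome.

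Section 9.8, on what the TSC and the funder may weigh beside the primary outcome when deciding on Phase 3, says: "This will include the following secondary outcome measures: absolute weight change (kg); % of participants achieving" ≥5% weight loss, and then ≥10%. Section 2.1 is similar: "The TSC in discussion with NIHR may consider other core outcome criteria e.g. absolute weight change (kg); health inequalities; % of men achieving" ≥5% or ≥10% weight loss. It adds that the study could end before 42 months if the agreed criteria are not met.

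For analysis, Section 9.3.3 provides a suitable generalised linear model, "including binary logit regression for dichotomous outcomes (e.g. smoking status) and ordered logit for ordinal outcomes (e.g. alcohol intake"). It adds: "Statistical significance will be at the 2.5% level". It does not say which of the two models applies to the weight-loss bands.

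**The concern.** There are two linked problems.

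First, Section 9.8 describes ≥5% loss as a secondary outcome, but the section that defines the secondary outcomes does not contain it. Which outcomes are secondary is for the protocol to fix, and two of its sections disagree. The outcome concerned is one that may inform whether the 24-month phase goes ahead.

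Second, a bounded band is a poor responder outcome. A man who improves from 4% to 6% loss leaves the 0–<5% band and counts there as a non-event. A man who improves from 9% to 11% leaves the ≥5–<10% band in the same way. Men also enter each band from below. The net change in a band therefore depends on where the control distribution lies, and an odds ratio for the band need not point towards benefit. If each band has its own logit test at the 2.5% level, an intervention that works as planned could show no difference, or an apparently adverse one, on a named secondary outcome.

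**Working it through.** **Inputs from the protocol (Section 9.1).** Difference 3.3 kg (3% of 109 kg), SD 8 kg, two-sided alpha 2.5%, 90% power, 146 men followed up per arm, 25% loss to follow-up. Feasibility Study SD at 12 months: 4.9 to 6.3 kg.

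**Inputs assumed.** Percentage weight loss is normally distributed with equal SD in the arms. The control-arm mean loss is not given in the protocol and is varied from −1% (a gain) to 2%.

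**The plan's own figure.** n = 2 × (8/3.3)² × (2.2414 + 1.2816)² = 145.9, so 146 per arm. 146/0.75 = 194.7, so 195 per arm and 585 in total. The stated sample size reproduces.

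**SD on the percentage scale.** 8/109 = 7.3%. The Feasibility Study range is 4.9/109 = 4.5% to 6.3/109 = 5.8%. The values used are 7.3% (planning) and 5.5% (inside the Feasibility Study range).

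**Band probabilities.** With mean loss m and SD s:
- P(0–<5%) = Φ((5 − m)/s) − Φ((0 − m)/s)
- P(≥5–<10%) = Φ((10 − m)/s) − Φ((5 − m)/s)
- P(≥5%) = 1 − Φ((5 − m)/s)

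Control has mean m and the intervention arm m + 3.

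**Power.** Φ(|d|/SE − 2.2414), where d is the difference in proportions and SE = √[p₁(1 − p₁)/146 + p₂(1 − p₂)/146].

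Each cell shows control → intervention, with power in brackets.

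| SD | Control mean loss | 0–<5% | ≥5–<10% | ≥5% cumulative |
|---|---|---|---|---|
| 5.5% | −1% | 29.0 → 34.9 (12%) | 11.5 → 22.0 (57%) | 13.8 → 29.3 (85%) |
| 5.5% | 0% | 31.8 → 34.9 (5%) | 14.7 → 25.7 (54%) | 18.2 → 35.8 (89%) |
| 5.5% | 1% | 33.9 → 33.9 (1%) | 18.3 → 29.0 (48%) | 23.4 → 42.8 (91%) |
| 5.5% | 2% | 34.9 → 31.8 (5%) | 22.0 → 31.8 (37%) | 29.3 → 50.0 (93%) |
| 7.3% | −1% | 24.0 → 26.7 (4%) | 14.0 → 20.4 (22%) | 20.6 → 34.1 (65%) |
| 7.3% | 0% | 25.3 → 26.7 (2%) | 16.1 → 22.3 (18%) | 24.7 → 39.2 (68%) |
| 7.3% | 1% | 26.3 → 26.3 (1%) | 18.3 → 24.0 (15%) | 29.2 → 44.6 (70%) |
| 7.3% | 2% | 26.7 → 25.3 (2%) | 20.4 → 25.3 (11%) | 34.1 → 50.0 (71%) |

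Taking the SD as exactly 8/109 (7.34%), or using a slightly different power formula, lowers the smallest ≥5% power to about 64%.

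The 0–<5% band is exactly unchanged at a control mean of 1%, whatever the SD, because means of 1 and 4 lie symmetrically about the band's midpoint of 2.5. Below 1% the band rises, and above 1% it falls. The odds ratio runs from 0.87 to 1.31.

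**The case against.** The protocol never says outright that the bands are tested separately. Section 9.3.3 offers ordered logit as well as binary logit and assigns neither to the bands. The summary gives the bands in one run, which could be read as a single ordered outcome. Assigning models to variables is commonly left to the SAP, which is not shown here. This stands: separate tests are the plain reading of outcomes listed as percentages of participants, but they are not established. The second part of the point is therefore conditional.

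A reader might infer that both bands can miss a real effect entirely. The figures do not support that. The ≥5–<10% band rises in every scenario above, and would be flat only at a control mean loss of 6%. At a smaller SD it can do well: with SD 4.5% and control mean 0% it goes from 12.0% to 26.8%, with power 84%. Only the 0–<5% band is flat or reversed in the range considered.

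A reader might also infer that the progression rule depends on ≥5% loss. Section 2.1 makes the primary outcome the criterion and says the TSC may consider others. The firmer wording in Section 9.8 only lists what that optional consideration covers.

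Nor is information lost. The ≥5% count is the sum of two listed, mutually exclusive categories. Absolute change, ≥10%, any loss and any gain are reported alongside, so a fall in the 0–<5% band would not be read alone. Finally, the protocol claims power only for the mean difference, so low power for a band is not in itself an error.

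None of this removes the disagreement between Sections 4.4.2 and 9.8.

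**Conclusion.** The inconsistency is established from the text alone: Section 9.8 names a secondary outcome that Section 4.4.2 and the summary do not list. It should be corrected.

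The statistical part holds on the condition that each band is tested as its own dichotomous outcome. Under the planned 3-point effect, the 0–<5% band then changes by about −3 to +6 percentage points with power 1–12% and has no fixed direction of benefit. The ≥5–<10% band does rise, by 5 to 11 points with power 11–57%. It is much less sensitive than cumulative ≥5%, which rises by about 13 to 21 points with power about 64–93%.

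These sizes rest on normality, SD 5.5–7.3%, an assumed control mean loss of −1 to 2%, 146 men analysed per arm and alpha 2.5%. The lack of a fixed direction follows from the band having an upper limit. The exact sizes depend on the assumptions. The primary outcome is not affected.

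**What to change.** In Section 4.4.2 and the trial summary, list the percentage achieving ≥5% and the percentage achieving ≥10% weight loss as the secondary responder outcomes, in the same terms as Sections 2.1 and 9.8. Keep the bands either as descriptive counts or as one ordinal outcome analysed by the ordered logit that Section 9.3.3 already provides, and say which. Settle this before the 12-month results are seen.

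The cost is wording in the protocol and matching wording in the SAP. The same weight data serve, and the primary analysis and sample size stay as they are. The only loss is separate p-values for the bands.
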